### 2.3 Study design

In this hybrid type 1 mixed methods implementation study we use a quasi-experimental design. The CONSORT Extension for pragmatic trials with its checklist was used (47). A single intervention municipality will be given access to the Nutrition Now resource and another control municipality (non-equivalent control) will continue as normal (**Figure 2**). Data from participants resident in the intervention municipality will be collected in the form of a pretest before they are given access to the Nutrition Now resource. Subsequently post-test data will be collected until the child reaches 2 years of age (See Data collection). Participants in the control municipality will be asked to provide pre- and post-test data but will not receive access to the Nutrition Now resource. Additionally, a time-series design will be used for comparisons within the intervention municipality between groups of participants exposed to the Nutrition Now resource at different levels of duration, and different types of exposure (See Data collection).

Enrolment started September 2022. The anticipated recruitment period is from September 2022-to April 2023, and we envision that the last participant (if recruited in early pregnancy in April 2023) will complete the study in September 2025. The ECECs were recruited prior to September 2022 and MCH personnel and parents will be recruited autumn 2022.

Intervention municipality provision of access to the Nutrition Now resource starts upon enrollment in the study and is expected to continue beyond the study period as long as the municipality finds it useful.

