The sample size in this study is capped by the annual birth rate in the two municipalities (~400 per group, e.g., a total of approx. 800 births each year). The primary effectiveness outcome, aspects child diet quality, exemplified by vegetable intake was used to check that the study would be sufficiently powered. In a previous efficacy trial of 298 1–2-year-olds, we observed a difference in the change from baseline to 6-month follow-up of +0.46 vegetable items per day in favour of the intervention group (n=148). Assuming a participation rate in this study between 50 and 80%, we anticipate a sample size of 510-820 from each municipality, of whom 100-160 will have potentially been exposed to all parts of the Nutrition Now resource (*in utero* to 2-years of age). The worst-case scenario, with a 50% participation rate and 100 participants being exposed to all parts of the Nutrition Now resource, would enable us to detect a difference in vegetable of intake between groups of 0.5 items per day (alpha of 0.05 and 80% power). We anticipate that several hundred participants will be exposed to the intervention to some extend enabling other comparisons between the intervention and control municipality, with larger participant numbers.

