**Figure 4 f4:**
[figure not shown]
Overview of timeline for data collection, and exposure to the Nutrition Now resource (consisting of e-learning resources targeting different phases in a child’s 1000 first days) in the intervention municipality in the effectiveness trial. Pregnant women and parents of children between 0-2 years of age will be recruited from October 2022 until April 2023 through the MCH centre route. Participants will be exposed to age-appropriate content of the Nutrition Now resource and will be asked to respond to successive age-specific digital questionnaires depending on whether they are pregnant or the child’s age. Participants are given access to the Nutrition Now resource after completing the first questionnaire (pretest). ECEC staff will be recruited and complete the pretest questionnaire in September 2022, before getting access to the Nutrition Now-recourse. The post-test ECEC-staff questionnaire will be distributed seven months into the implementation of the intervention.

Consenting pregnant women (at any time during pregnancy), and parents of children between 0-2 years (at any time in this age interval) will first be asked to complete a short digital questionnaire to provide socio-demographic data in addition to expected due date (for pregnant women), or child’s age (for parents). Thereafter they will be asked to complete a second questionnaire tailored to the age of the child. Access to the Nutrition Now resource will be provided when the age-specific questionnaire is completed. The dose and duration of exposure to the Nutrition Now resource will differ between the participants depending on when they enter the study. Only those who are pregnant when entering the study between October 2022 and April 2023 will potentially be exposed to the whole range of intervention content, whereas a 1-year-old whose parent(s) enter the study in the same period, will be exposed to the “Toddlers 1-2 years” component and, if in ECEC, also the “Preschoolers 1+ years” component (**Figure 4**). Two-year-olds recruited at the regular health visit will be given access to the “Toddlers 1-2 years” component after completing the 24 months questionnaire.

ECEC leaders and staff will respond to questionnaires when consenting to participate in the study and seven months after getting access to the Nutrition Now resource.

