Participants (both parents and ECEC staff) recruited in the control municipality will be asked to complete the same questionnaires as intervention participants but will not have access to the Nutrition Now resource.

Data on food purchase history in the ECECs will be collected from both the ECECs in the intervention and control municipality, for the years 2022 and 2023, to obtain data on fruits and vegetables purchases. Municipal budget data for 2022 and 2023 will be collected to gather info on municipal spend on activities related to early childhood nutrition and feeding practices in both the intervention and control municipality.

*Quantitative and qualitative data will be collected to evaluate the implementation process and outcomes*. Quantitative data from parents and ECEC staff at seven and 12 months after being enrolled in the study, will be collected using questionnaires with items from the seven implementation outcomes described in **Table 1**. Additional data will be collected using checklists during iterative interviews with ECEC and MCH during the first six months of the project, and usage data will be collected from the Nutrition Now resource. Evaluation of acceptability, appropriateness, and feasibility of the Nutrition Now resource will be done using a validated and generic questionnaire developed by Weiner et al. (41).

Qualitative data will be collected from short iterative interviews with team leaders in ECEC and contact persons for MCH nurses and midwifes, to promote self-reflection and continuous development. Further, focus group discussions with ECEC and MCH staff will be conducted approximately seven months after start of the implementation period to explore experiences with the implementation strategies. Individual interviews with ECEC leaders and stakeholders at municipality level will also be conducted (**Table 1**).

In depth description of what motivates and/or hinders use of the Nutrition Now resource will be explored in ethnic minority groups to render the next version of the resource more inclusive. With an anthropological way of interviewing, multi-stage, in-depth, open-ended and ethnographic interviews will be conducted with sub-samples of pregnant women and parents within ethnic minority groups in the intervention municipality to understand how the implementation of the resource works in and affects their everyday life.

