### 2.9 Analysis

#### 2.9.1 Effectiveness

Evaluating our effectiveness objective requires following a treatment policy estimand strategy (59, 60)- that is the effect of access to the Nutrition Now resource regardless of post-enrolment or intercurrent events such as non-compliance or discontinuation. This necessitates that outcome data be collected regardless of level of engagement and assumes that missing data are missing not at random (MNAR). Statistical models appropriate for de facto estimands will thus be used and the effect of MNAR on our effectiveness estimates will be assessed using sensitivity analyses. Confounding due to the non-randomised nature of the study, e.g., household size and income, parental education, ECEC status (public or private), will be assessed and adjusted for using regression models.

The main comparison will be between children and parents given access to all Nutrition Now components and those in the control municipality. Similar estimators of the Nutrition Now effectiveness will be available from comparisons within the intervention municipality since we will have data on approximately 100 parent-offspring pairs completely unexposed to the Nutrition Now resource as a result of the recruitment design (described above). The latter comparisons will improve causal inference by triangulating the evidence from two designs with different sources of bias (61). In this example they act as a sensitivity analysis to assess bias from residual confounding.

The recruitment strategy also creates variation in the number of components of the Nutrition Now resource each observational unit will be exposed to. Combined with the serial data collection points (pregnancy, 6 weeks, 6, 12, 18 and 24 months), we will be able to assess the effectiveness of each component of the resource in addition to duration of access.

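### For child diet, the between-municipality and within-municipality comparisons each leave one bias in; data already being collected would support an added difference-in-differences

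*Protocol article*

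**What the plan says.** Section 2.3 describes a quasi-experimental design with one intervention municipality and one non-equivalent control. "Participants in the control municipality will be asked to provide pre- and post-test data", and section 2.8 adds that those "recruited in the control municipality will be asked to complete the same questionnaires as intervention participants". Section 2.5 opens the study to the same 0-2-year age range in both places.

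Section 2.9.1 names the main comparison (all components versus the control municipality) and adjusts for confounding by regression on covariates such as household size, income, parental education and ECEC status. It adds a comparison with about 100 unexposed pairs in the intervention municipality, which serves as a sensitivity analysis for residual confounding: "The latter comparisons will improve causal inference by triangulating the evidence from two designs with different sources of bias".

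Section 2.8 states who can be fully exposed: "Only those who are pregnant when entering the study between October 2022 and April 2023 will potentially be exposed" to the full content. It also says that two-year-olds recruited at their health visit get access only after they have completed the 24-month questionnaire.

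On power, section 2.5 says that the worst case, with "100 participants being exposed to all parts of the Nutrition Now resource", would allow the study to "detect a difference in vegetable of intake between groups of 0.5 items per day" ("alpha of 0.05 and 80% power"). The benchmark from the earlier efficacy trial is a "difference in the change from baseline to 6-month follow-up of +0.46 vegetable items per day".

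**The concern.** The design is introduced as pretest/post-test, but the main comparison cannot use a pretest of the primary outcome. Mothers of fully exposed children complete their first questionnaire in pregnancy, before there is any child diet to measure. What remains is one municipality against one other at a given child age. Covariates measured on families cannot remove features shared by a whole municipality. Table 2 shows such features: 1 versus 6 health centres (a recruitment route), and 178 versus 62 persons per square kilometre.

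The internal comparison avoids the place difference but takes on a time difference, because the unexposed and the fully exposed reach 24 months about two years apart. Infant feeding can shift: the Introduction reports near-daily pouch use at 6 months rising from none in 2008 to 61% in 2020.

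If the two comparisons agree, a reader may conclude that residual confounding is small. That does not follow. The effectiveness conclusion is meant to inform scale-up.

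**Working it through.** **Inputs.** Section 2.5 gives alpha 0.05 (sidedness not stated; two-sided assumed), power 80%, 0.5 items/day, and 100 fully exposed (up to 160). Section 2.9.1 gives about 100 unexposed pairs. The article does not give the SD, the control group size used for the power statement, or the size of the early control cell. I assume 100 for both sizes.

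**1. The plan's own figure.** Detectable difference = (1.960 + 0.842) × SD × √(2/100). Setting this to 0.50 gives SD = 0.50 / (2.802 × 0.1414) = 1.26, and SE = 1.262 × 0.1414 = 0.1785. The statement therefore fits a plain two-group comparison with SD 1.26, but without a stated SD it cannot be verified. Control groups of 160, 200 or 510 would imply SD 1.40, 1.46 or 1.63; a one-sided test with 100 per group would imply 1.42.

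**2. What each comparison estimates.** Let I and C be the intervention and control municipalities, 0 the two-year-olds measured at recruitment, and 1 the pregnancy-enrolled children at 24 months. Let τ be the effect, a the municipality difference left after covariates, and b the calendar change.
- Main: I1 − C1 = τ + a
- Internal: I1 − I0 = τ + b
- Main minus internal = a − b, so agreement shows a ≈ b, not that both are zero. The two also share I1 (correlation 0.5 with equal cells).
- Difference-in-differences: (I1 − C1) − (I0 − C0) = τ, if a is the same in both periods and I0 is unexposed.

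**3. Timing.** Two-year-olds are measured from October 2022 to April 2023, midpoint about mid-January 2023. The fully exposed reach 24 months from about October 2024 to the stated end in September 2025, midpoint about April 2025. The gap is about 2.2 years. An assumed trend of 0.1 items/day per year would by itself give about 0.1 × 2.2 = 0.22 items/day in the internal comparison.

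**4. Main comparison when τ = 0.** Type I error = 1 − Φ(1.96 − a/0.1785) + Φ(−1.96 − a/0.1785). Assumed values of a of 0.1, 0.2 and 0.3 items/day give about 9%, 20% and 39%. If municipalities instead vary randomly with SD t, SE = √(0.1785² + 2t²).
- t = 0.10: SE 0.228, detectable difference 0.64, true error about 12%.
- t = 0.20: SE 0.334, detectable difference 0.94, true error about 30%.

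The values of a and t are illustrations. The 0.64 and 0.94 should not be compared with step 6, which has no municipality-by-period term.

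**5. Agreement.** Simulation with SD 1.26, 100 per cell, τ = 0 and a = b = 0.3: both planned comparisons average 0.30, and both are significant in favour of the intervention in 23% of trials (about 0.5% when a = b = 0). Difference-in-differences averages 0.00 and rejects in 5%.

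**6. Precision of the difference-in-differences.** SE = 1.262 × √(4/100) = 0.252, and 2.802 × 0.252 = 0.71. With equal cells this is √2 × 0.50 whatever the SD. Power at 0.5 is Φ(0.5/0.252 − 1.96) = 51%; at 0.46 it is 45%. With 160 per cell the detectable difference is 0.56 and power at 0.5 is 71%. About 200 per cell would restore 80%. If some 300 early questionnaires per municipality could be pooled over ages (assumed), SE = √(0.1785² + 1.262² × 2/300) = 0.206 and the detectable difference is 0.58.

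**7. Is I0 clean?** Section 2.8 has ECEC staff in the intervention municipality complete their pretest in September 2022 and then receive access, while parents are recruited through health centres from October 2022 to April 2023. Table 2 gives 85% of 1-2-year-olds in ECEC. A two-year-old recruited in early 2023 may already have had months of the ECEC component. The share in participating ECECs is not stated.

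**The case against.** The strongest reply is that the quoted sentence is correct: one comparison is biased by place, the other by time. A reader might infer that the triangulation claim is false or that neither comparison can identify the effect. The documents support neither inference. Each comparison identifies the effect under its own assumption: no residual municipality difference for the main one, no calendar change for the internal one.

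Difference-in-differences also has an untestable assumption, parallel trends. With one municipality per arm it cannot separate a local shock from the effect. Its cells differ in selection too: pregnancy-enrolled children have passed through about two years of possible dropout, two-year-olds at recruitment through none. That cancels only if dropout is similar in both municipalities, although only one receives the resource and reminders. Because I0 may be partly exposed, the early municipality gap may contain some treatment effect, and subtracting it would pull the estimate towards zero. A reader might take that gap as a direct measure of residual confounding; step 7 shows why it is only an indicator.

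Finally, the article is condensed. It leaves the models open, gives its confounders as examples, and acknowledges non-equivalence and possible selection bias between sites. An analysis plan not shown may already contain the extra contrast.

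All of this stands and limits the claim. What remains is that the article itself names the main comparison and its sensitivity analysis, and that those two leave a and b unseparated although the fourth cell is collected.

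**Conclusion.** This is a worthwhile, low-cost improvement rather than an error. For child diet, the main comparison has no pretest and cannot separate the effect from a fixed municipality difference that the covariates miss. The internal comparison cannot separate it from about two years of calendar change. Agreement between them is weaker evidence than it appears.

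The sizes are conditional: SD 1.26 is back-solved, the municipality differences and trend are assumed, and the early control cell is taken as 100. That the unexposed group consists of two-year-olds measured before access is inferred from the only such route that section 2.8 describes. The point concerns child diet; maternal and pregnancy-stage measures can have a pretest.

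A reader might go further and want the difference-in-differences to replace the internal comparison or become the main analysis. The figures do not support that: with 100 per cell, power at 0.5 items/day is about 51%, and replacement would discard a check whose bias is of a different kind.

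**What to change.** Keep both planned comparisons and prespecify one supporting analysis: (pregnancy-enrolled at 24 months minus two-year-olds at recruitment, intervention) minus (the same, control), with the same covariates.

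- Report the early same-age difference between municipalities as an indicator of residual municipality difference.
- State that the main confidence interval assumes no residual municipality-level difference.
- Record recruitment date and attendance at a participating ECEC. Repeat the analysis in children not in participating ECECs, and in those recruited earliest. Apply the same check to the group that the plan treats as wholly unexposed.
- Make pooling of early questionnaires across ages secondary, since it assumes a municipality gap that is constant over age.
- State the parallel-trends and similar-dropout assumptions, and that a municipality-specific shock cannot be removed.

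The cost is analysis-plan wording, one further model and at most two recorded items; the outcome data are already being collected. The price in precision is a detectable difference of about 0.71 items/day with 100 per cell, or about 0.58 if some 300 early questionnaires per municipality can be pooled, against 0.50 for the plain comparison. Specifying it before outcome data are seen prevents the choice of contrast from following the results.

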#### 2.9.2 Implementation

*Quantitative:* We will report descriptive statistics for implementation outcomes assessed quantitatively [acceptability, appropriateness, feasibility, adoption and reach (**Table 1**)]. In addition, the number of people accessing the webpage, and sub-pages, and the time spent there, will be automatically registered in the Nutrition Now-resource. *Qualitative* interview data will be transcribed verbatim and coded deductively informed by the CFIR framework (62) and inductively to capture issues within and outside of this framework. We will use these findings to inform future scale-up at county level.

#### 2.9.3 Economic evaluation

We will conduct economic evaluation in two ways. First, we will perform a within-trial economic analysis to evaluate the cost-effectiveness of the trial, i.e., trial-specific intervention costs relative to intervention effect on the outcomes selected for the economic evaluation. The within-trial analysis will be a cost–utility analysis (CUA), estimating the incremental cost per quality-adjusted life years (QALYs) gained from being given access to the Nutrition Now resource. QALYs will be generated *via* measurement of utility values based on the Pediatric Quality of Life Inventory (PedsQL) Infant Scales (13-24 months) (38), a pediatric generic health-related quality of life (HRQoL) instrument. Additionally, cost-effectiveness analysis (CEA) will be performed by calculating incremental cost per unit developmental improvement measured with the widely used developmental screening tool, Ages & Stages Questionnaire (ASQ), validated for use in the Norwegian population (39, 63) (**Additional File 2, Table S2**).

Second, a decision analytic model will be used to model the potential long-term cost-effectiveness of the Nutrition Now intervention over a lifetime horizon. We will develop a birth cohort simulation model based on estimated exposure-outcome associations in the Norwegian Mother, Father and Child Cohort (64) to explicitly model a set of causal pathways known to link child development to diverse later life outcomes. The model will provide a framework for integrating effectiveness measures from the current study in addition to data from external studies, drawn from targeted literature searches. The decision analytic modelling will adopt a wider societal perspective.

### 2.10 Data management

A data management plan (DMP) has been developed and will be published elsewhere. The DMP is an ongoing document throughout the project period and is in accordance with Norwegian Research Council’s (NRC) guidelines. We plan to share anonymized data in the UiA data repository Dataverse. This will be done no later than upon acceptance for publication of the main findings from the final dataset. We will retain our data for five years after data collection has stopped. Hence, our data will be made open access in line with the NRC’s guidelines, prior to three years after the completion of the study. Standard meta-information about the data will be uploaded.

Data from the pregnant women and parents of 0–2-year-olds will be collected using digital questionnaires created and distributed electronically using an encrypted version of the web-tool “Nettskjema” linked to a secure server, the Service for Sensitive Data (TSD, in Norwegian, “Tjeneste for Sensitive Data”). TSD is constructed for storing and processing data in agreement with the Norwegian Personal Data Act and Health Research Act (65). Digital questionnaires created in “Nettskjema” will also be used to collect data from leaders and other staff in the ECEC.

## 3 Discussion

There are several potential challenges the project may face. Recruitment of participants and their continued participation is crucial for both the implementation and effectiveness part of this study. To reduce participant burden and maximise retention, we will keep the questionnaires short, easily comprehensible, and easy to complete. To avoid missing all data in the case of partly completed questionnaires, it will be possible to respond to only a few initial core questions, and still participate. Further, selection bias at recruitment between intervention and control sites may bias intervention estimates. In addition, although the original interventions have shown promising results in previous studies, the impact of the interventions might be more modest in a real-life setting. This dilution of intervention effect is a common finding in effectiveness studies and implementation trials (66), however the iterative approach to the implementation in our study is meant to reduce the chance of such dilution (54, 66).

A major strength of this study is the established efficacy in the original four interventions, the co-creation with the municipality, ECECs and MCH undertaken, and the established capacity and networks built by the research team. This experience will help address challenges along the way. The municipality setting and organization of ECEC and MCH are quite similar in all parts of Norway and thus, we expect that our findings related to the implementation will be generalizable to other Norwegian municipalities. Further, focusing on culturally diverse groups both in the effectiveness and implementation part, will render more culturally diverse and sensitive resources for future approaches.

*Nutrition Now* will break new ground by (i) systematically implementing and evaluating cumulative effects of successive dietary interventions in the first 1000 days of life in a real-life context, (ii) maximising interdisciplinary collaboration and integrating an anthropological approach with quantitative methods to truly adapt the intervention to context, (iii) bridging the previously described evidence-to-practice gap through rigorous scientific effectiveness evaluation of municipal implementation, (iv) harnessing the benefits of digital, video-based, technology to optimise access to dietary guidance in the municipalities, and (v) taking advantage of existing settings across sectors in municipal care to secure universal reach.

Lifecourse research has tended to be skewed towards epidemiology rather than implementation, and commonly target single transitional phases (67). Our project addresses these scientific shortcomings by implementing and evaluating evidence-based e-learning resources across multiple transitions early in life in a real-world community setting. Few developed interventions proven successful in controlled experimental settings are used to their full potential. Our study integrates four efficacious dietary interventions comprising e-learning resources and applies them in a municipal care setting. If this approach demonstrates public health benefit without increasing care providers’ workload it may provide a valuable contribution to other fields of lifecourse research.

Norway alone has the potential to save 14.8 billion EUR annually in health costs from improvements in population diet (68). According to Norwegian public health law, municipalities and counties are responsible for providing sound public health advice on diet and nutrition (69). MCH nurses and midwives are in a key position to guide parents on diet and nutritional issues, but often lack resources and time (70). ECEC staff are also strategically important as they are responsible for care of children while their parents work or study. Our digital diet interventions (70–72) offer a low-cost complementary tool for public health work in municipalities, and if successfully adapted when scaled-up, have the potential to improve population diet and health and respond to the need for tools and improved skills in childcare and ECECs. By gaining in-depth understanding of factors critical for successful local implementation, we will be ready to advance to county and national implementation, thereby contributing significantly to evidence-based health services in all municipalities in Norway.

